### Data collection and outcomes

The study evaluates the impact of statin prescription on two primary outcomes:

*HRQoL*, measured by the Patient-Reported Outcomes Measurement Information System 10-Question Short Form (PROMIS-10), which includes subscales for mental health and physical health.^39 40^*Three-point MACE-free survival*, defined as survival without any of the following MACEs: cardiovascular death, non-fatal myocardial infarction or non-fatal stroke. MACE events are self-reported by participants or reported by a proxy using a calendar returned every 3 months and are verified annually with treating physicians.

Secondary outcomes include functional outcome assessed using the modified Rankin Scale^41^; falling using a falls calendar; cognitive functioning using the Montreal Cognitive Assessment (MoCA)^42^ or the Telephone version of MoCA^43^; quality-adjusted life-years (QALYs) based on the EuroQol 5-Dimension 5-Level (EQ-5D-5L)^44^ questionnaire; and societal costs using The Older Persons and Informal Caregivers Survey–Minimum DataSet (TOPICS-MDS).^45^

At baseline, demographics, medication use and recent clinical metrics and laboratory values are extracted from the electronic patient record by local investigators. Furthermore, the PROMIS-10, MoCA, EQ-5D-5L, TOPICS-MDS and CFS are assessed. Follow-up continues for 24 months, with an optional 1-year extension for early enrollees. Assessment frequencies vary by outcome measure (figure 1). Participants, caregivers and local investigators are not blinded. However, all follow-up is conducted by investigators from the central research team who are blinded to treatment allocation.

**Figure 1 F1:**
[figure not shown]
Visual representation of the study design. *Control physician. **Info from physician/pharmacy. CFS, Clinical Frailty Scale; EQ-5D-5L, EuroQol 5-Dimension 5-Level questionnaire; MACE, major adverse cardiovascular event; MoCA, Montreal Cognitive Assessment; ASAT, Aspartate Aminotransferase; ALAT, Alanine Aminotransferase; mRS, modified Rankin Scale; PROMIS-10, Patient-Reported Outcomes Measurement Information System 10-Question Short Form; TIA, transient ischaemic attack; (T-)MoCA, Telephone version of Montreal Cognitive Assessment; TOPICS-MDS, The Older Persons and Informal Caregivers Survey–Minimum DataSet.

Adherence to the intervention is monitored using pharmacy records. To minimise participant burden and enhance engagement, follow-up is conducted by phone or post, with no extra clinic visits or tests. The primary outcome (PROMIS-10) is relatively brief, which facilitates high completion rates. When questionnaires returned by post are incomplete, participants or their proxies are contacted by telephone to obtain the missing information. The study team will make repeated attempts when necessary to ensure that key outcomes are collected as completely as possible. At 12 and 24 months, general practitioners provide the most recent laboratory and blood pressure data available from routine care. Measurements performed within 6 months of the follow-up time point are accepted. Additionally, the SAFEST-RCT is part of the ‘Versneld Evalueren’ (Accelerated Evaluation) pilot by the national programme Care Evaluation and Appropriate Use (‘*Zorgevaluatie en Gepast Gebruik*’), which promotes rapid evaluation and implementation of healthcare innovations.

### Patient and public involvement

This study is supported by the Dutch Brain Injury Association (Hersenletsel.nl). A patient representative from the association was closely involved from the early stages of the study, including the overall study design, and the selection of outcome measures and questionnaires. The burden of the intervention and time investment for participants were jointly assessed with the representative and association members. The association will also assist in disseminating the results through their website and relevant patient channels.

### Sample size

We hypothesise that in frail older patients with recent ischaemic stroke or TIA, starting statins will cause a clinically relevant decrease in HRQoL without substantially improving MACE-free survival. For HRQoL, we expect baseline PROMIS-10 subscale scores of approximately 45, with an SD of 9.0 and a Minimal Clinically Important Difference of 4.5, approximated as 0.5 SD.^46 47^ Frailty and prior ischaemic stroke or TIA both reduce life expectancy in older adults.^11^,^13^ Based on previous studies, we estimate a 2-year survival rate of 52% in the control group.^48^,^50^ Cardiovascular events increase with age, and this older, frail cohort is therefore at higher baseline risk for MACE. Statin use in secondary prevention after ischaemic stroke or TIA in people of all ages has shown reductions in recurrent stroke (HR 0.89), myocardial infarction (HR 0.55) and cardiovascular death (HR 0.78).^51^ For our composite outcome of MACE-free survival in frail older patients, higher baseline risk and limited life expectancy support an HR estimate of 0.70. A total of 612 participants provide 99% power to detect a >4.5-point decrease in HRQoL and 80% power to detect an HR of 0.70 for MACE-free survival, using a two-sided alpha of 0.05, and accounting for 5% loss to follow-up.^52^ Loss to follow-up is expected to be minimal, as most discontinuations will involve study outcomes (MACE or non-cardiovascular death), and partial follow-up still contributes to the time-to-event analysis.

Sample size calculations are based on the Hotelling Lawley Trace test, using a linear exponent autoregressive model with a base correlation of 0.5 and a decay of 0.3.^53^ With approximately 6800 eligible patients annually in the Netherlands based on Dutch health insurance data,^54^ we expect to reach our recruitment target.

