## Introduction

### Background

 Age is a major risk factor for ischaemic stroke and transient ischaemic attack (TIA).^1^ With the global population ageing rapidly, the global incidence of these conditions is expected to rise by 81% between 2021 and 2050.^2^ Ischaemic stroke is a leading cause of disability and generates significant economic burden.^1 3^ As individuals who have suffered an ischaemic stroke or TIA are at increased risk for subsequent cardiovascular events,^1 4 5^ secondary prevention is deemed essential.^6^

Statins are a key component of secondary prevention and have been proven effective in middle-aged patients who had a stroke and TIA.^6 7^ Due to their higher baseline risk, the absolute benefit of statins is expected to be greater in older individuals. However, due to the under-representation of frail older patients in statin trials, there is limited evidence regarding the effectiveness and safety of statins in this population.^8^

A recent meta-analysis of 28 randomised controlled trials (RCTs), including the Pravastatin in elderly individuals at risk of vascular disaese (PROSPER) trial, the Heart Protection Study (HPS) and the Justification for the use of statin in prevention: an intervention trial evaluating rosuvastatin (JUPITER) trial, showed that statins used for secondary prevention lowered the annual incidence of major adverse cardiovascular events (MACE) from 5.8% to 4.8% in people aged 70–75 years, and from 6.8% to 6.0% in people over 75 years.^7^ However, the 17 trials that included older participants excluded individuals with conditions such as multimorbidity, cognitive impairment, life expectancy of less than 5 years, severe heart failure, chronic liver or kidney disease or uncontrolled diabetes. This likely restricted the inclusion of frail individuals. Given that frailty affects approximately 20% of community-dwelling adults aged over 70, 31% of those over 80 and 51% of those over 90 years,^9^ the exclusion of this subgroup creates a substantial evidence gap.

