While it might be tempting to extrapolate the benefits of statin therapy from fit to frail older patients, substantial differences between these populations must be acknowledged. In frail older adults, it is essential to consider time to benefit.^10^ Both frailty and a history of ischaemic stroke or TIA independently reduce life expectancy in older individuals, and their combination further worsens prognosis.^11^,^13^ Although lipid lowering and plaque stabilisation can occur within months after starting statin therapy,^14^ a full reduction in cardiovascular events typically requires years.^15^ The results of a meta-analysis indicated that 2.5 years of statin therapy are needed to prevent one MACE per 100 adults aged 50–75.^15^ Consequently, frail older stroke survivors with limited life expectancy may not live long enough to fully benefit from statin therapy.

Frailty also increases the risk of adverse effects.^16^ Statins can cause muscle pain, myopathy, elevated liver enzymes and diabetes mellitus.^17 18^ No significant association has been found between statin use and adverse cognitive effects.^19^ However, the under-representation of frail older individuals in clinical trials may have led to an underestimation of the full spectrum of statin-related risks. Age-related changes in pharmacokinetics and pharmacodynamics, comorbidities and polypharmacy further elevate the risk of adverse effects and drug interactions in this population.^20^,^24^ Even mild adverse effects like myopathy can severely impact mobility, increase fall risk and reduce quality of life (QoL) in frail individuals.^25^ While older adults often prioritise health-related quality of life (HRQoL), daily functioning and independence over mortality,^26 27^ statin trials typically focus primarily on outcomes such as recurrence of cardiovascular events and mortality.^28^ A recent systematic review and meta-analysis by our group found no conclusive evidence that statin use improves QoL or functional status in older patients following ischaemic stroke or TIA.^29^ Furthermore, an RCT involving individuals with a life expectancy of less than 1 year found that discontinuation of statin therapy was associated with improvements in QoL.^30^

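### The 80% power for MACE-free survival rests on a 52% survival figure that does not appear to match the defined endpoint, and on an HR of 0.70 whose stated rationale is unsupported

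*Protocol article*

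**What the plan says.** The Sample size section of the protocol article gives one control-arm rate: "we estimate a 2-year survival rate of 52% in the control group". It comes directly after a sentence on shortened life expectancy. No control MACE rate is given.

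For the effect, the section cites all-age results after stroke or TIA, "reductions in recurrent stroke (HR 0.89), myocardial infarction (HR 0.55) and cardiovascular death (HR 0.78"), and then states that "higher baseline risk and limited life expectancy support an HR estimate of 0.70" for the composite. It concludes that 612 patients give "80% power to detect an HR of 0.70 for MACE-free survival", "using a two-sided alpha of 0.05", with an allowance of 5% for loss to follow-up.

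The Data collection and outcomes section defines the endpoint by cardiovascular death, non-fatal myocardial infarction (MI) and non-fatal stroke. The Sample size section, however, names non-cardiovascular death next to MACE as a study outcome.

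The Background cites a meta-analysis in which statins for secondary prevention lowered annual MACE from 5.8% to 4.8% at ages 70-75 and "from 6.8% to 6.0% in people over 75 years".

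**The concern.** Two inputs carry the 80%, and each is open to question.

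- **Event rate.** An overall-survival figure includes non-cardiovascular deaths, which three-point MACE does not count, and leaves out non-fatal events, which it does count. It cannot stand in for a MACE-free rate without further assumptions.
- **Hazard ratio.** The two reasons given for 0.70 run against the protocol's own Background. That section links higher baseline risk to a larger absolute benefit, which does not by itself make a hazard ratio stronger. It also says that the full reduction in events usually takes years and that these patients may die before gaining it fully. That argues for a weaker effect over 2 years.

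The trial's hypothesis is that statins will not substantially improve MACE-free survival, and the results are meant for national guidelines. If power is well below 80%, a non-significant MACE result would seem to confirm the hypothesis while saying little, and the stated 80% would make it look informative.

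**Working it through.** **Inputs from the protocol.** N = 612, 1:1 allocation, two-sided alpha 0.05, 80% power, HR 0.70, 5% loss, 24 months of follow-up, control survival 52%.

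**1. The protocol's own figure.**
- Events (Schoenfeld) = 4 × (1.960 + 0.842)² / (ln 0.70)² = 246.8, so 247.
- Event proportions if 52% is event-free survival: control 0.48; statin 1 − 0.52^0.70 = 0.367; mean 0.4236.
- Patients = 246.8 / 0.4236 = 582.5. Multiplied by 1.05 this is 611.7, so 612. (Dividing by 0.95 gives about 613-614.)
- Power with 612 × 0.95 = 581.4 patients: 581.4 × 0.4236 = 246 events; Φ(√246.3 / 2 × 0.3567 − 1.960) = 79.9%.

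The claim therefore reproduces with 52% as 2-year MACE-free survival.

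**2. If 52% is overall survival and only three-point MACE counts.** The all-cause hazard is −ln(0.52)/2 = 0.327 per year. Let s be the cardiovascular share of deaths and r the annual non-fatal MACE hazard. Both are assumptions, with s = 40-70% and r = 0.05-0.10. With constant hazards, MACE hazard m = 0.327s + r and competing hazard c = 0.327(1 − s), the 2-year incidence is m/(m + c) × [1 − exp(−2(m + c))]. The statin arm uses 0.70m.
- s = 40%, r = 0.05: incidence 25.4% and 18.7%; 128 events; power 52%.
- s = 70%, r = 0.10: incidence 44.2% and 33.8%; 227 events; power 77%.

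**3. If 52% is overall survival, all deaths count, and statins act only on the MACE part at 0.70.** Overall HR = (0.70m + c)/(m + c).
- s = 40%, r = 0.05: HR 0.856; 292 events; power 26%.
- s = 70%, r = 0.10: HR 0.769; 307 events; power 63%.

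**4. The hazard ratio against the protocol's own figures.**
- 0.70 is stronger than two of the three component HRs (0.89 and 0.78). Equal weighting gives (0.89 + 0.55 + 0.78)/3 = 0.74, or 0.73 on the log scale.
- Older-adult MACE ratios: 4.8/5.8 = 0.83 and 6.0/6.8 = 0.88.

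**5. Power (%) with 581.4 evaluable patients**, statin-arm proportion 1 − (1 − control)^HR:

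| Control 2-year incidence | HR 0.70 | HR 0.78 | HR 0.83 | HR 0.88 |
|---|---|---|---|---|
| 25% | 51.6 | 29.5 | 18.9 | 11.3 |
| 35% | 66.1 | 39.3 | 24.9 | 14.2 |
| 48% | 79.9 | 51.1 | 32.5 | 18.0 |

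At 48% events, HR 0.74 gives 66%.

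**The case against.** The strongest reply is that the sum is correct and that the protocol nowhere says the 52% is overall survival. The cited sources are not at hand. If they report MACE-free survival, the 80% stands for HR 0.70 and only the label is wrong. The match at 612 is good evidence of how the figure was used, but not proof: it depends on inflating by 1.05. All this stands, so the reading of 52% as overall survival is an inference from wording and position.

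The endpoint wording can also be read as being alive and free of MACE. If all deaths count, 48% is a floor for control events and the calculation in step 2 does not apply. The protocol also attaches 0.70 to the composite itself, so the dilution in step 3 is an alternative assumption and not the protocol's. That too stands, and it is why the two sections need reconciling.

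On the HR, 0.70 lies inside the cited component range because MI is 0.55. The ratios 0.83 and 0.88 are crude ratios of annual rates, from trials that the Background says probably kept frail people out. The statement that "2.5 years of statin therapy are needed to prevent one MACE per 100 adults" concerns absolute risk at ages 50-75, so it is not used here as evidence for a weaker HR.

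A reader might go further and infer that the design cannot deliver 80% power, or that the MACE result will be non-significant whatever the truth. The documents do not support either. At a true HR of 0.70, power is 52-77% in step 2 and about 80% with 48% events, so significance is then the more likely result.

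**Conclusion.** The concern holds as a fault in the inputs and not in the arithmetic. The 80% is right only for a 48% control event proportion and HR 0.70. The 48% comes from a figure that appears to describe a different endpoint, and the protocol is inconsistent on whether non-cardiovascular death is an event.

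If the 52% is overall survival, power at HR 0.70 is about 52-77% when only three-point MACE counts (control incidence about 25-44%, about 128-227 events). It is about 26-63% when all deaths count and the benefit is confined to MACE (overall HR about 0.77-0.86). These ranges rest on the assumed cardiovascular share of deaths, the assumed non-fatal rate and constant hazards; none of these is in the protocol.

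The HR of 0.70 is optimistic but not excluded. The rationale offered for it is unsupported, because the protocol's Background points the other way. At 48% events, power is about 33% at 0.83 and 18% at 0.88.

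**What to change.** In the Sample size section:

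1. State what the 52% measures.
2. Reconcile the endpoint definition with the mention of non-cardiovascular death as a study outcome, and say whether such a death is a primary event.
3. State the assumed 2-year control incidence of the endpoint actually analysed and the events required (247 for HR 0.70).
4. Replace the single 80% with power across HR 0.70-0.88 and control incidence of about 25-48%.
5. Delete the claim that higher baseline risk and limited life expectancy support 0.70, and justify the chosen HR another way or present it as an optimistic scenario.
6. Say that a non-significant MACE result will be interpreted from the confidence interval of the HR and not from a claim of 80% power.

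This is a text change. The stated power becomes less favourable, and no extra patients are needed.

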This study has several limitations. First, its open-label design may introduce bias, as patients’ awareness of their treatment allocation could influence the perceived benefits, adverse effects and responses to the patient-reported PROMIS-10 questionnaire, which is the primary outcome in this study. This design was chosen to minimise patient burden by avoiding placebo use and to prevent confusion in medication management, which is particularly important in frail older adults. The direction and magnitude of this potential bias are uncertain; participants’ beliefs about their treatment may affect questionnaire responses either positively or negatively. To minimise bias, outcome assessments are conducted by study team members who remain blinded to treatment allocation. Second, the exclusion of individuals unable to provide informed consent, such as those with severe cognitive impairment or disabling aphasia, may limit the generalisability of findings to the most severely affected populations. Third, the exclusion of patients unable to communicate in Dutch may introduce bias, as non-Dutch-speaking residents could have a different profile of stroke risk factors and comorbidities. To minimise this risk, patients with limited Dutch proficiency are allowed to participate with support from a proxy. Fourth, adherence to statin therapy will be assessed through pharmacy dispensing records, which reflect prescription collection but not actual medication intake. This approach was chosen to minimise participant burden in this frail population, in which more direct methods, such as blood tests, pill counts or adherence questionnaires, as described in the review of López-Pineda *et al*,^59^ were not feasible. Fifth, in the intervention group, the choice of statin type and dose is left to the treating neurologist according to routine care and the Dutch Stroke guideline, which may introduce some heterogeneity in treatment. Lastly, the study focuses solely on statin therapy and does not consider other lipid-lowering agents such as ezetimibe, bempedoic acid or proprotein convertase subtilisin/kexin type 9 inhibitors, which may be explored in future research.

In summary, the SAFEST-RCT and its complementary cohort study aim to fill a critical evidence gap in the management of statin therapy in frail older adults after ischaemic stroke or TIA, to provide essential guidance for clinical decision-making in this vulnerable and understudied population.

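### Two primary outcomes are each powered at the full two-sided 0.05 with no multiplicity rule stated, which puts the chance of a false primary claim at about 9–10% or more, and the article elsewhere names only one primary outcome

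*Protocol article*

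**What the plan says.** All references are to the protocol article.

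- **Data collection and outcomes** introduces the endpoints with "The study evaluates the impact of statin prescription on two primary outcomes": HRQoL and three-point MACE-free survival. It describes the PROMIS-10 as an instrument "which includes subscales for mental health and physical health".
- **Sample size** plans HRQoL at subscale level: "we expect baseline PROMIS-10 subscale scores of approximately 45". The spread and target difference that go with this are given as follows: "with an SD of 9.0 and a Minimal Clinically Important Difference of 4.5, approximated as 0.5 SD". The section then makes two power claims. The HRQoL claim reads "A total of 612 participants provide 99% power to detect a >4.5-point decrease in HRQoL". The claim for the other endpoint reads "80% power to detect an HR of 0.70 for MACE-free survival". A single error level serves both of these claims: "using a two-sided alpha of 0.05, and accounting for 5% loss to follow-up".
- **Statistical methods, Primary outcomes** analyses both endpoints: HRQoL by a repeated-measures mixed model with deceased patients scored 0 and two-sided 95% intervals, and MACE-free survival by Cox regression.
- **Discussion**, in the limitation on open-label design, says of the PROMIS-10: "which is the primary outcome in this study". The text below Figure 1 in Data collection and outcomes also refers to the PROMIS-10 as the primary outcome in the singular.

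No section says how alpha is shared, which outcome is tested first, or whether one or both must be significant.

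**The concern.** There are two linked problems.

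1. **Error rate.** A significant result on either outcome could carry a practice message: lower HRQoL would support withholding statins, and a MACE benefit would support starting them. With each tested at 0.05 and no rule joining them, the chance of at least one false primary claim exceeds 5%. It rises further if each PROMIS-10 subscale can support the HRQoL claim.
2. **Naming.** The outcome list and the analysis section treat both endpoints as primary, while two other places give that status to the PROMIS-10 alone. A reader of the results could not tell from this text whether MACE-free survival is a primary or a supporting endpoint. The article says the results will be integrated into Dutch national guidelines, so this matters.

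**Working it through.** **Inputs.** From Sample size: N = 612, 5% loss, two-sided alpha 0.05, HR 0.70, control 2-year survival 52%, subscale mean about 45, SD 9.0, difference 4.5. From Participants: 1:1 allocation. Assumption: the 52% is read as control MACE-free survival.

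**Step 1. Reproduce the plan's MACE figure.**
- Schoenfeld events: 4(1.960 + 0.842)² / (ln 0.70)² = 247.
- Treated event-free proportion: 0.52^0.70 = 0.633. Mean event probability: (0.480 + 0.367)/2 = 0.4236.
- 247/0.4236 = 584; 584/0.95 = 615, against 612 stated.
- In reverse: 612 × 0.95 ≈ 581 evaluable; 581 × 0.4236 = 246 events. Power = Φ(√246 × 0.3567/2 − 1.960) = 79.9%, against 80% stated.

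**Step 2. Was an equal split built in?**
- At alpha 0.025, 246 events give Φ(√246 × 0.3567/2 − 2.241) = 71.1%.
- Keeping 80% at 0.025 needs 299 events: 299/0.4236 = 706; 706/0.95 = 744.
- So 612 uses the full 0.05 for MACE-free survival.

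**Step 3. Error rate with one HRQoL test plus MACE.**
- Independent: 1 − 0.95² = 9.75%.
- Deaths scored 0 on HRQoL, some of them cardiovascular, link the two tests. From 1 − P(|Z₁| < 1.96 and |Z₂| < 1.96) for bivariate normal statistics, an assumed correlation of 0.3 gives 9.5% and 0.5 gives 9.0%.

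**Step 4. Error rate with two subscale tests plus MACE.**
- Independent: 1 − 0.95³ = 14.3%.
- MACE independent, subscale correlation 0.5, 0.7, 0.9: 13.6%, 12.9%, 11.7%.
- Shared zeros raise the subscale correlation. For death proportion π, survivor mean 45, SD 9.0 and survivor correlation r (assumed 0.5–0.7), it is [(1 − π)·81·r + π(1 − π)·45²] / [(1 − π)·81 + π(1 − π)·45²].
  - π = 0.48: (21.06 + 505.44)/547.56 = 0.96 for r = 0.5, and 0.98 for r = 0.7.
  - π = 0.20: (32.4 + 324)/388.8 = 0.92 for r = 0.5, and 0.95 for r = 0.7.
- At subscale correlation 0.96, the chance of at least one false positive is 11.0% with MACE independent and 9.4% with an HRQoL–MACE correlation of 0.7.
- A patient-level null simulation (290 per arm, shared zeros, 15% non-fatal MACE assumed, 40–100% of deaths cardiovascular assumed) gave about 8.5–11.4%.

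**Step 5. Does HRQoL have alpha to spare?** Single-visit normal approximation, Φ(d√(n/2) − z). The plan's Hotelling–Lawley calculation cannot be rebuilt, because the article text gives neither the number of visits in it nor the contrast.
- Survivors only: 290 × 0.52 ≈ 151 per arm, d = 4.5/9.0 = 0.5. Power is 99.1% at 0.05 (stated 99%) and 98.2% at 0.025.
- Deaths scored 0, equal mortality, 290 per arm:
  - π = 0.48: SD = √547.56 = 23.4, difference 0.52 × 4.5 = 2.34, d = 0.10. Power is 22% at 0.05 and 15% at 0.025.
  - π = 0.20: SD = √388.8 = 19.7, difference 3.6, d = 0.18. Power is 59% at 0.05 and 48% at 0.025.

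**The case against.** **The SAP may settle it.** A protocol article often leaves multiplicity to the SAP, and a full 0.05 per outcome in a power statement is compatible with a fixed test order, which would control the error without changing N. This stands as a limit on the point: if such an order exists, stating it closes the error-rate part. But the article does fix two primary outcomes at one alpha, with 95% intervals for HRQoL and no rule joining them, and an unseen SAP does not remove the contradiction in naming.

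**The two outcomes answer different questions.** The stated hypothesis pairs an HRQoL loss with no substantial MACE gain, and whether distinct hypotheses reported separately need family-wise control is debated. That is fair. However, the pairing is not a rule that both must be significant, so it does not hold the error at 5%.

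**Stronger readings the text does not support.**
- A reader might infer three primary tests, any of which makes the trial a success. The article states no such rule. Separate subscale tests are implied by the subscale-level planning, but the analysis section does not prescribe them.
- A reader might take 14% as the expected error. It is the value under independence, and shared zeros make the two subscales nearly one measure.
- A reader might infer from the 99% power that HRQoL can give up alpha at almost no cost. At 0.005 per subscale, power of 94–95% holds only when survivors are counted (151–159 per arm). With deaths as 0, the same approximation gives about 5% (48% deaths) to 27% (20% deaths). A split of 0.01 to HRQoL and 0.04 to MACE is therefore not supported.
- The singular wording occurs in remarks on questionnaire length and open-label bias, not in the analysis rules. It needs correcting, but it is not evidence of an intention to choose the headline later.

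**Conclusion.** The point holds. As written, the plan carries about a 9–10% chance of at least one false primary claim with one HRQoL test, and about 10–14% if both subscales are tested separately, most plausibly 10–11% given the zeros for deaths. These figures assume both nulls are true, jointly normal test statistics, and assumed correlations within and between outcomes. Strong HRQoL–MACE dependence can take the result somewhat below the quoted ranges (8.5% at the lowest in the simulation), still well above 5%. The reproduction of 612 also rests on reading the 52% as MACE-free survival.

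The contradiction over one or two primary outcomes needs no calculation and stands whatever the SAP says. Both matters should be corrected, and neither calls the design into question.

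**What to change.** 1. Name both primary outcomes consistently: in the outcome list and the text below Figure 1 in Data collection and outcomes, and in the open-label limitation in the Discussion.
2. Define the HRQoL claim as one test: either one named subscale, or a stated joint rule for both.
3. Before unblinding, specify a Holm or Hochberg procedure, or a fixed test order, across HRQoL and MACE-free survival at overall two-sided 0.05. If the SAP already does so, state it in the protocol.

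**Cost.** The change is to wording in the protocol and SAP, and N stays at 612. With Holm or Hochberg, MACE power is about 71% (alpha 0.025) if HRQoL is not significant, and stays at 80% if it is. HRQoL is likewise tested at 0.025 when MACE is not significant. That costs little among survivors (99.1% to 98.2%) but more under the planned scoring of deaths (59% to 48% at 20% deaths, 22% to 15% at 48%, single-visit approximation). With a fixed order neither test loses alpha, but a claim on the second outcome is possible only if the first is significant.
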